### Randomization and masking

We will use simple randomization to allocate participants to one of two sequences of interventions: Group A: personalized care program followed by active control; or Group B: active control followed by personalized care program. The study coordinator (NM) conducted the randomization using a randomized table generator (GraphPad Software Inc, La Jolla, CA). Randomization will be concealed; no other study personnel will be aware of the intervention assignments. However, it was not possible to blind the study coordinator (NM) as they are one of the main treating clinicians. Additionally, it was not possible to ensure adequate blinding of the participants, given the necessary thorough description of the treatment procedures that occurred during the informed consent process.

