As an additional element, participants’ cognition will be specifically examined through a rapid advanced quantitative electroencephalogram (EEG) via the NeuroCatch™ brain vital sign framework. Conventional EEG and event-related potentials (ERP) methods and analysis are time-consuming and typically restricted to controlled laboratory settings. This makes its use to help objectively guide a clinician’s management decision inaccessible to routine clinical use. Hajra et al. (2016) have detailed the framework of the brain vital sign in young and older individuals [25]. The framework translated well-established ERP responses into a portable, rapid, automated and easy-to-use evaluation method. It also incorporates a normative existing comparison framework analogous to existing vital sign metrics, such as that for blood pressure. Quantitative EEGs have repeatedly shown that concussions cause objective measurable changes in brain activity and therefore the functions of the structures from which they originate [26]. Specifically, Fickling et al., (2019) showed abnormal ERPs in elite male junior hockey players acutely following a concussion [27]. They also observed persistent impairments in ERP, specifically P300, at the time of return to play. Fickling et al. (2019) also found that players who did not sustain a concussion during the season still demonstrated abnormal ERPs (N400) at the end of the season, representing possible cognitive impairment as a result of cumulative subconcussive impacts [27]. Additionally, Ozen et al. (2013) demonstrated, in young adults who sustained a concussion a minimum 1-year before testing, a negative correlation between abnormal ERP (decreased amplitude of P300) and lingering impairments in cognitive processing, memory, and concentration [28]. NeuroCatch™ is a portable quantitative EEG and will be performed at the KITE Innovations and Rehabilitation Clinics. NeuroCatch™ acquires and reports on event-related potentials (ERPs) derived from electroencephalogram (EEG). As part of the brain vital sign framework, three ERPs (brain vital sign), auditory N100 (auditory sensation); auditory oddball P300 (basic attention); and auditory speech processing N400 (cognitive processing) will be evaluated.

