### Statistical analysis

The primary outcome is a change in symptoms following rehabilitative interventions using the RPQ. Previous research examining the internal construct validity of the Rivermead Post-Concussion Symptom Questionnaire suggested that a score of 2 or more on at least 3 of the 16 symptoms represents an unfavourable outcome [40]. We chose to calculate the study sample size by assuming an effect size. Unfortunately, to date, no validated change scores exist, thus we prescribed a cut-off of 15% improvement as minimal clinically importance difference (MCID). This translates into a change of 2 points on the RPQ-3 and a change of 8 points on the RPQ-13. This agrees with prior clinical literature examining changes post-intervention on concussion symptoms [41]. Based on this effect size, a power of 80%, a significance level at *p* < 0.05 and a two-sided t-test, we calculated that a sample size of 50 participants was necessary [42].

Descriptive statistics will be applied to all outcome measures to assist in summarizing the results. Participant demographic data will be compared to assess compatibility between groups, specifically before the crossover point.

The statistical analysis conducted in this research is composed of an adjusted model using an analysis of variance to test for associations between variables and outcomes (two groups [personalized care or usual care] x 3 times [baseline, week 6 and 12]) [42]. The statistical analysis conducted in this study will be made using SAS OnDemand for Academics 2021. The data set is composed of six variables, two independent variables –personalized care group or usual care group – and four dependent variables – age, sex, and result of treatment on the RPQ graded as total score and sub-classification (RPQ-3 and RPQ-13). A 2-way analysis of covariance (ANCOVA) (two groups [personalized care or usual care] x 3 times [baseline, week 6 and 12] x baseline secondary outcomes [ERPs, NDI and PHQ-9] will be used to examine the effects of the rehabilitation programs while controlling for these covariates. Lastly, an unpaired t-test will be used to assess the effects of the rehabilitation programs on the secondary outcomes. In addition to the per-protocol analysis, an intention-to-treat analysis will be conducted.

All unintended effects, harms and/or dropouts during the program will be recorded.

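### Baseline RPQ enters both planned models only as a level of time, not as a covariate, while the ANCOVA adjusts for at least five other baseline measures and age and sex are called dependent variables

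*Protocol article*

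**What the plan says.** The Statistical analysis section of the protocol article defines the primary outcome as a change in RPQ and describes two models for it. The first is an ANOVA with two groups and three times, baseline being one of the times. The second is an ANCOVA with the same two factors, for which "baseline secondary outcomes [ERPs, NDI and PHQ-9] will be used to examine the effects of the rehabilitation programs while controlling for these covariates". The Secondary outcomes section counts three ERPs (N100, P300, N400), so with NDI and PHQ-9 there are at least five covariates. Baseline RPQ is not among them, although Table 1 schedules RPQ-3 and RPQ-13 at baseline. Neither model is labelled primary.

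The same section describes the data set as having "four dependent variables – age, sex, and result of treatment on the RPQ" scores.

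On the EEG, Assessments / procedures says that NeuroCatch "is a portable quantitative EEG and will be performed at the KITE Innovations and Rehabilitation Clinics". Population allows therapy at that site or at the Pain and Wellness Centre. Study design and Table 1 schedule the EEG at baseline, 6 weeks and 12 weeks without restriction by site.

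The trial is sized by "a significance level at *p* < 0.05 and a two-sided t-test" at 80% power, and "we calculated that a sample size of 50 participants was necessary". Allocation is by simple randomization.

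**The concern.** Baseline score on the outcome scale is usually the strongest predictor of the later score, and here it is scheduled for everyone. The article publishes an explicit covariate set that adjusts RPQ for the other baseline outcome measures but not for RPQ itself. With about 50 people and simple randomization, chance imbalance in baseline RPQ is a real possibility. A change-from-baseline contrast does remove that imbalance, but it subtracts the full baseline difference whatever the correlation, and so over-corrects when ρ is below 1. Adjusting for baseline RPQ subtracts only the part that predicts follow-up.

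Precision on the main RPQ comparison is at stake. There is also a possible loss of participants from the ANCOVA wherever a baseline ERP is missing. Separately, the label given to age and sex leaves their role in the adjusted model undefined.

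**Working it through.** **Inputs from the document.** Two-sided 5% significance, 80% power, a t-test and 50 participants in total (Statistical analysis). On the raw effect: "This translates into a change of 2 points on the RPQ-3 and a change of 8 points on the RPQ-13". Allocation is simple randomization to two sequences, taken here as 25:25.

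**Inputs assumed.** The document gives no SD, standardized effect or baseline-to-follow-up correlation. I use a standardized effect d = 0.8 and ρ from 0.3 to 0.8.

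**The plan's own figure.** N = 50 cannot be derived from the stated inputs, because a raw difference without an SD fixes no sample size. It is matched by d = 0.8:
- Normal approximation: n per group = 2(1.960 + 0.842)²/0.8² = 15.70/0.64 = 24.5, so 25 per group and 50 in total. The exact t-test gives 52.
- d = 0.8 corresponds to an SD of 10 on RPQ-13 (8/10) or 2.5 on RPQ-3 (2/2.5). With an SD of 8 on RPQ-13 the total would be 32, and with 12 it would be 72. The match therefore makes d = 0.8 a working value and does not confirm it.

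**Variance of the week-6 contrast.** Week 6 is the last assessment before the crossover. With n per group and a common SD σ, the variance of the estimated group difference is (2σ²/n) × f, where:
- group-by-time contrast with baseline as a time level (difference in change): f = 2(1−ρ)
- week-6 score with baseline RPQ as covariate: f = 1−ρ²
- week-6 score ignoring baseline: f = 1

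The ratio of the second to the first is (1−ρ²)/[2(1−ρ)] = (1+ρ)/2, which is below 1 for every ρ below 1.

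**Power.** The noncentrality is 0.8/√(2f/25), with 48 df for the change contrast and 47 df with baseline RPQ as covariate. At ρ = 0.5, for example, it is 0.8/√0.08 = 2.83 as planned and 0.8/√0.06 = 3.27 adjusted.

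| ρ | f as planned | f adjusted | Power as planned | Power adjusted |
|---|---|---|---|---|
| 0.3 | 1.40 | 0.91 | 64.9% | 82.7% |
| 0.5 | 1.00 | 0.75 | 79.1% | 89.2% |
| 0.6 | 0.80 | 0.64 | 87.3% | 93.4% |
| 0.7 | 0.60 | 0.51 | 94.7% | 97.2% |
| 0.8 | 0.40 | 0.36 | 99.2% | 99.6% |

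Ignoring baseline altogether gives 79.1% at every ρ, so below ρ = 0.5 the planned contrast does worse than not using baseline at all. Simulation (4,000 runs per setting, n = 50) agrees. At ρ = 0.5 it gave 79–80% as planned and 88–89% adjusted. At ρ = 0.7 it gave 94–95% and about 97%.

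In participants, 50 people analysed with baseline RPQ as covariate are worth 50 × 2/(1+ρ) under the planned contrast: 77 at ρ = 0.3, 67 at 0.5 and 59 at 0.7.

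**Cost of the five listed covariates.**
- In a week-6-only model, five uninformative covariates inflate the expected variance by 1 + 5/(50−5−3) = 1.12 and lower power from 79.1% to 74.3%. If they are prognostic they can raise it (81% to 90% in the simulations).
- In the planned repeated-measures layout, a covariate that is constant over time and entered as a main effect left the group-by-time estimate unchanged in a test fit (−0.701, SE 0.361, with and without it). A cost arises there only if covariates are crossed with time or if missing values remove participants.
- Once baseline RPQ is in the model, adding five more covariates at ρ = 0.5 moved simulated power from 88–89% to 85–88.5%. They bring no gain there and may bring some loss.

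**The case against.** The best defence is that baseline RPQ is in fact used. Baseline is a level of time in both models and the outcome is defined as change, so a reader who inferred that the plan throws baseline RPQ away would be wrong. That stands, and it is why the loss is measured against the change contrast and not against an analysis that ignores baseline.

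Three other strong readings are tempting and also fail:
- **The ANCOVA as the primary analysis.** The article does not say so. The ANOVA comes first, and the ANCOVA may be supportive. The point survives because neither model has baseline RPQ as a covariate.
- **A power gain from about 80% to between 89% and 97%, growing with ρ.** This takes a t-test on week-6 scores as the comparator. The Statistical analysis section assigns the unpaired t-test to the secondary outcomes. Against the planned layout the gain shrinks as ρ grows.
- **Participants at the second site lacking ERPs and dropping out of the model.** The text names where the EEG is performed but schedules it for everyone, and those treated elsewhere may attend the named site for it. Missing ERPs are a possible risk and not a stated fact. The document gives no missing rate, so I put no size on it.

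It is also fair to say that the age and sex wording may be a labelling slip in a model the article calls adjusted. It has no shown numerical effect but still needs correcting.

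**Conclusion.** The concern holds in a limited form. Baseline RPQ is used as a response level where it would serve better as a covariate, the listed covariates are a poor substitute for it, and age and sex are mislabelled. On the week-6 contrast the cost is about 18 power points at ρ = 0.3 (82.7 − 64.9), 10 at ρ = 0.5 (89.2 − 79.1) and 2.5 at ρ = 0.7 (97.2 − 94.7).

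These sizes rest on an assumed d of 0.8, an assumed ρ, equal groups and equal variances at baseline and week 6. They cover the first-period comparison only, not the full 12-week crossover. The direction does not depend on d: for any ρ below 1, adjusting for baseline RPQ has the smaller variance. A repeated-measures model that constrained the groups to a common baseline mean would recover most of this efficiency, but the article describes no such constraint. The documents do not support a claim that the number of covariates alone costs precision, or that participants will be lost by site.

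**What to change.** In the Statistical analysis section:
1. Model post-baseline RPQ-3 and RPQ-13, each with the baseline score of the same sub-scale as covariate, and take baseline out of the time factor for that model.
2. Remove age and sex from the dependent variables and list them as covariates.
3. Keep baseline ERPs, NDI and PHQ-9 for the responder-prediction analysis that the Objectives section already sets as the tertiary aim, or for a sensitivity model. A missing baseline ERP then cannot remove a participant from the RPQ analysis.
4. State where participants treated at the Pain and Wellness Centre have their EEG.

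The cost is wording only. RPQ is already scheduled at baseline, and no visit, measure or participant is added. The change should be fixed before outcome data are examined by group.

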**Methods:**

We will conduct a multi-center 12-week case-crossover randomized controlled trial. 50 participants will be recruited from out-patient University Health Network clinics and community-based clinical practices around the greater Toronto area. Participants will be randomized at baseline to Group A: a personalized care program followed by an active control or Group B: an active control followed by a personalized care program. Participants will be included should they be 21 years of age and older and have symptoms that have persisted beyond 4 weeks but less than 1 year. Participants will undergo 6-weeks of care in their respective streams. After 6-weeks, participants will undergo a re-examination. They will then crossover and undertake the alternative treatment for 6 weeks. At the end of 12 weeks, participants will undertake the endpoint examinations. The primary outcome will be the Rivermead Postconcussion Questionnaire (RPQ). The secondary outcomes will be changes in standardized clinical examination, Neck Disability Index (NDI), Patient Health Questionnaire (PHQ-9) and an electroencephalography (EEG) via NeuroCatch^™^. The statistical analysis to be performed is composed of an adjusted model using an analysis of variance, specifically using an unpaired t-test to test for associations between variables and outcomes.

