### Study design

We will be conducting a 12-week case-crossover randomized controlled trial (see Table 1). At baseline, following the standardized examination, completion of the primary outcome measure (RPQ), baseline quantitative EEG and secondary outcome measures (NDI and PHQ-9), participants will be randomized to either Group A: a personalized care program followed by an active control or Group B: an active control followed by a personalized care program. No washout period will be used between interventions. It was assumed that given both interventional groups have a focus on rehabilitative therapy that no wash-out period was needed. Participants will undergo 6 weeks of care in their respective streams. After 6 weeks, participants will undergo a re-examination. They will then crossover and undertake the alternative treatment for 6 weeks. At the end of 12 weeks, participants will undertake the endpoint examinations.

**Table 1 Tab1:** Enrolment schedule, interventions and assessments

	Study Period						
	Enrolment/Baseline assessment	Allocation	T1	Mid-point assessment (6 weeks)	Cross-over	T2	End-point assessment (12 weeks)

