#### Secondary outcomes

The secondary outcome measures include a quantitative EEG measuring three ERPs (brain vital sign framework), the Neck Disability Index (NDI), and the Patient Health Questionnaire-9 (PHQ-9).

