### Patient Health Questionnaire-9 (PHQ-9)

A screening form for depression and anxiety via the PHQ-9 will be administered. The PHQ-9 has been shown to have adequate reliability and good validity for the concussion population as well as the spinal pain population [36–39].

All outcome measures will be compared to participants’ values at baseline, 6-week re-assessment and trial end-point assessment.

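### The unpaired t-test named for the secondary outcomes leaves collected baseline and within-person information unused, and the abstract presents it as the adjusted main analysis

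*Protocol article*

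**What the plan says.** Under Secondary outcomes the article lists its measures: "The secondary outcome measures include a quantitative EEG measuring three ERPs (brain vital sign framework), the Neck Disability Index (NDI), and the Patient Health Questionnaire-9". The section on the PHQ-9 closes by saying that all outcome measures will be compared with "participants’ values at baseline, 6-week re-assessment and trial end-point assessment", and Table 1 schedules NDI, PHQ-9 and EEG at those three visits.

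Study design describes a two-period crossover. After six weeks on the first programme, "They will then crossover and undertake the alternative treatment for 6 weeks". The same section adds: "No washout period will be used between interventions".

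Statistical analysis names three procedures:

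- an ANOVA of two groups by three times;
- an ANCOVA that adds "x baseline secondary outcomes [ERPs, NDI and PHQ-9] will be used to examine the effects of the rehabilitation programs while controlling for these covariates";
- for the secondary outcomes, a separate last item: "an unpaired t-test will be used to assess the effects of the rehabilitation programs on the secondary outcomes". No covariate, period or participant term is attached to it.

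The abstract's Methods paragraph describes the analysis as an adjusted ANOVA model, "specifically using an unpaired t-test to test for associations between variables and outcomes", and does not limit the t-test to secondary outcomes.

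**The concern.** An unpaired t-test takes two independent sets of values and adjusts for nothing. This trial collects two things that such a test leaves out: a baseline value of every secondary outcome, and a result under each programme from the same person. Baseline ERPs, NDI and PHQ-9 do enter the plan as covariates, but in the ANCOVA, which is listed apart from the t-test on those same measures.

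With 50 participants, unused information matters. Cognition measured by EEG is the stated secondary aim, and the Background notes that earlier trials recruited too few participants for adequate power. The likely cost is wide intervals and missed effects on neck disability, mood and EEG.

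Separately, a reader of the abstract would take the t-test to be the adjusted main analysis. The Methods give that role to the ANOVA and ANCOVA.

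**Working it through.** **Inputs.** From the article: 50 participants, two sequences, two periods of six weeks, three visits, no washout. Assumed: 25 per sequence (randomization is simple, so the split may differ), equal standard deviations (SD) at each visit, and the correlations below, which the article does not give. Standard errors (SE) are in SD units and power uses the normal approximation.

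**The plan's own figure.** The article states no number for the secondary outcomes. Its sample size of 50 is for the RPQ and gives no SD, so it cannot be derived from the stated inputs. It fits a two-group comparison at a standardized effect of about 0.80: 2(1.96 + 0.84)²/0.80² = 24.5, so 25 per group. Here it supplies only the group sizes.

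**Reading 1: the sequences are compared at week 6 (25 v 25).** The observations are independent, so the test is valid. With r the correlation between baseline and week 6:

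- raw scores: SE = √(2/25) = 0.283
- change from baseline: SE = 0.283 × √(2(1 − r))
- own-baseline ANCOVA: SE = 0.283 × √(1 − r²)

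ANCOVA leaves 1 − r² of the raw-score variance, so it removes r². Against change scores it leaves (1 − r²)/(2(1 − r)) = (1 + r)/2.

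| r | SE raw | SE change | SE ANCOVA | variance removed v raw | variance removed v change | power for 0.5 SD: raw | power for 0.5 SD: ANCOVA |
|---|---|---|---|---|---|---|---|
| 0.3 | 0.283 | 0.335 | 0.270 | 9% | 35% | 42% | 46% |
| 0.5 | 0.283 | 0.283 | 0.245 | 25% | 25% | 42% | 53% |
| 0.6 | 0.283 | 0.253 | 0.226 | 36% | 20% | 42% | 60% |
| 0.7 | 0.283 | 0.219 | 0.202 | 49% | 15% | 42% | 70% |

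In SE terms, the excess of change scores over ANCOVA is 1/√0.75 = 1.15 at r = 0.5 and 1/√0.85 = 1.08 at r = 0.7.

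**Reading 2: results are pooled by programme over both periods (50 v 50 values from 50 people).** The two sets are not independent. With ρ the within-person correlation between periods:

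- SE the test would use: √(2/50) = 0.200
- SE that respects the pairing: √(2(1 − ρ)/50)
- ratio: 1/√(1 − ρ)
- actual type I error at nominal 5%: 2(1 − Φ(1.96/√(1 − ρ)))

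| ρ | paired SE | ratio | actual type I error |
|---|---|---|---|
| 0.4 | 0.155 | 1.29 | 1.1% |
| 0.5 | 0.141 | 1.41 | 0.6% |
| 0.6 | 0.126 | 1.58 | 0.2% |

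A simulation of 20,000 trials (25 per sequence, period effect 0.3 SD, no carryover) agrees. The pooled unpaired test had type I error 0.6% at ρ = 0.5 and 0.05% at ρ = 0.7. Its power for a 0.4 SD effect was 50% in both cases, against 79% and 94% for a two-sample test on within-participant period differences, which kept type I error near 5%.

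**Reading 3: the sequences are compared at week 12.** By then both have had both programmes without a washout, so the test cannot separate the current programme from what remains of the previous one.

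**Abstract against Methods.** Both name an adjusted ANOVA model. The abstract then specifies it as an unpaired t-test; the Methods specify it as two groups by three times and give the t-test to the secondary outcomes. An unpaired t-test is not an adjusted model and does not handle three time points, so the two descriptions do not agree.

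**The case against.** The strongest reply is that the article nowhere says the two periods are pooled. A reader might infer that the standard errors for the secondary outcomes are simply wrong, but the text does not support this. Unpaired fits a between-sequence comparison at least as well, and the article's comparison of demographics is placed before the crossover point. A week-6 comparison has a correct standard error. An unpaired t-test between sequences on within-participant period differences is also a valid crossover analysis, although nothing in the article describes it. This reply stands: the 1.29 to 1.58 ratios belong to Reading 2 alone.

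Nor is it certain that the baseline is ignored, since the closing line of the PHQ-9 section could mean change scores. That also stands as a possibility. The gain from ANCOVA is then the smaller one shown against change scores at r = 0.6 or 0.7, but it does not vanish.

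Two further inferences go too far. One is that the test will produce false claims of benefit: with positive correlation the pooled version is conservative. The other is that the test is the main reason effects would be missed. At week 6 with r = 0.5, power for 0.5 SD is still only 53% after the improvement, so much of that risk comes from 25 per sequence, and the article claims no power for these outcomes.

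Finally, calling the abstract a second, rival primary test reads too much into it. It looks like two Methods sentences run together. The mismatch is real, but it is one of wording.

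**Conclusion.** The point holds as one of inefficiency, an unfixed contrast and an inconsistent abstract. As written, the test for the secondary outcomes uses neither the pairing nor the own baseline, although both are available.

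On the week-6 reading it is valid and costs precision: 25% to 49% of the raw-score variance is avoidable for r from 0.5 to 0.7, or 25% to 15% if change scores are used. On the pooled reading independence fails and the test becomes conservative. All sizes rest on assumed correlations, and the article does not settle which reading applies. It concerns the secondary outcomes and the abstract's wording; it does not show that the RPQ analysis in the Methods uses the wrong test. It is worth correcting because the correction is nearly free.

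**What to change.** In Statistical analysis, replace the t-test sentence with wording such as: *NDI, PHQ-9 and each ERP measure will be compared between sequences at week 6 by ANCOVA, with the baseline value of the same measure as covariate. A two-period model with treatment, period and random participant will be reported as supportive; without a washout it assumes no differential carryover.*

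Week 6 should lead because carryover cannot yet have occurred. In a two-period, two-sequence design, carryover is aliased with sequence and can bias the treatment estimate, and both programmes include education and daily home exercise that may persist. The price is precision if there is in fact no carryover: at a correlation of 0.5 the week-6 ANCOVA has SE 0.245, against 0.141 for the paired comparison over both periods. That is a reason to report the crossover model too, not to lead with it.

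In the abstract, name the same main model as the Methods and drop the t-test as its specification. The cost is wording and minor programming, with no new data or visits.

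### The 2 x 3 ANOVA named for the RPQ sits badly with the promised intention-to-treat analysis: fitted classically it drops anyone missing week 12, and fitted row by row it ignores within-person correlation

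*Protocol article*

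**What the plan says.** The protocol article, under Statistical analysis, describes the RPQ model as an analysis of variance with the layout "two groups [personalized care or usual care] x 3 times [baseline, week 6 and 12". An ANCOVA on the same layout, with baseline ERPs, NDI and PHQ-9 added, "will be used to examine the effects of the rehabilitation programs while controlling for these covariates". The section gives the unpaired t-test to the secondary outcomes. The abstract words it differently, describing an analysis of variance "specifically using an unpaired t-test to test for associations between variables and outcomes".

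On analysis sets, the section says: "In addition to the per-protocol analysis, an intention-to-treat analysis will be conducted". On people who leave, it says: "All unintended effects, harms and/or dropouts during the program will be recorded".

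Study design fixes the timing: "After 6 weeks, participants will undergo a re-examination. They will then crossover and undertake the alternative treatment for 6 weeks". It also says "No washout period will be used between interventions". The week-6 RPQ is therefore the last score taken before anyone has received the other programme.

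**The concern.** An intention-to-treat analysis should use the outcome data collected from everyone randomised. A three-visit ANOVA in its classical repeated-measures form works on complete sets of visits. A participant who finishes the first period, gives a week-6 RPQ and then leaves in weeks 7 to 12 drops out of the whole analysis, including the week-6 comparison. What happens after the crossover then decides who counts in the only between-group comparison made before it. With no washout, that is also the only one free of carry-over.

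Leaving could plausibly differ by sequence. At crossover one group goes from twice-weekly to weekly sessions and the other goes the opposite way. Participants are not blinded, and they rate the RPQ themselves. The article gives no figures on leaving, so this is a reason for care and not a demonstrated effect.

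The other ordinary fit, one row per person per visit with a single error term, keeps the week-6 value. Its standard errors are wrong, because three scores from one person are handled as if they came from three people.

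**Working it through.** **1. The plan's own figure.** The stated inputs are 80% power, two-sided 5% significance, a t-test, 50 participants, and a target difference: "This translates into a change of 2 points on the RPQ-3 and a change of 8 points on the RPQ-13". No standard deviation is given, so 50 cannot be reproduced from the stated inputs alone. Assume 25 per group (no ratio is stated) and solve backwards:
- Normal approximation: d = (1.960 + 0.842) x sqrt(2/25) = 0.79.
- Noncentral t: d = 0.809.
- Implied SD from the t solution: 8/0.809 = 9.9 on RPQ-13 and 2/0.809 = 2.5 on RPQ-3.

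The abstract's recruitment target is also 50, so no allowance for dropout is visible.

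**2. Does the layout itself need all three visits?** In one simulated data set of 50 people (person SD 8, residual SD 6), 13 had no week-12 score.
- Listwise deletion: 50 - 13 = 37 people remain.
- One-row-per-visit ANOVA: 3 x 50 - 13 = 137 rows, with all 50 week-6 values used.
- Mixed model: the same 137 rows and all 50 week-6 values.

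The answer is therefore no. The loss comes from a listwise fit, not from the 2 x 3 layout.

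**3. Cost of the listwise fit in precision.** The dropout rates are assumed. Power is for a two-sample t-test at week 6 with d = 0.809.

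| Loss in each period | With week-6 RPQ | With all three visits | Power, all week-6 data | Power, listwise |
|---|---|---|---|---|
| 10% | 50 x 0.90 = 45 | 45 x 0.90 = 40.5 | 75.5% | 70.8% |
| 15% | 50 x 0.85 = 42.5 | 42.5 x 0.85 = 36.1 | 73.0% | 65.6% |

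At 10%, the standard error grows by sqrt(45/40.5) = 1.054, or about 5%. The fall from 80% to 75.5% is period-1 loss and occurs under any model. The part due to listwise deletion is 75.5 - 70.8 = 4.7 percentage points (7.4 points at 15%).

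**4. Possible bias of the listwise fit.** This was simulated with 25 per group, SD 10.1, a true week-6 difference of 8 points and about 20% lost before week 12. Where loss was informative, its log-odds changed by 0.8 per SD of week-6 change. All of these are assumptions.

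| Pattern of loss | Week-6 estimate in completers | Power, completers | Power, all 50 |
|---|---|---|---|
| Random | 8.0 | 68% | 79% |
| Depends on week-6 change, same direction in both groups | 7.4 | 65% | 78% |
| Depends on week-6 change, opposite directions by group | 5.2 | 38% | 78% |

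A milder scenario has 10% to 20% leaving one sequence only, with leaving correlated 0.3 to 0.5 with outcome. It shifts that group's week-6 mean by 0.06 to 0.17 SD, which is 0.06 x 9.9 = 0.6 to 0.17 x 9.9 = 1.7 RPQ-13 points.

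**5. Cost of the row-by-row fit.** With the SDs assumed in step 2, the within-person correlation is r = 64/(64 + 36) = 0.64. For complete data with equal correlation between visits:
- Group effect averaged over visits: the true standard error is sqrt(1 + 2 x 0.64) = 1.51 times the one reported, so the test is too liberal.
- Group difference in change between two visits: the reported standard error is 1/sqrt(1 - 0.64) = 1.67 times the true one, so the test is too conservative.

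**The case against.** A reader might infer that the ANOVA as written requires all three visits and that the intention-to-treat analysis is therefore a completers analysis. The documents do not support that. The article does not call the model repeated-measures, names no SAS procedure, states no complete-case rule and excludes nobody for lacking week 12. Step 2 shows that the same layout can keep every week-6 value. The abstract's unpaired t-test, if applied at week 6, would need no week-12 value either.

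A reader might also infer that because dropouts are said only to be recorded, no RPQ is collected once treatment stops. That is not supported either. The schedule sets the RPQ at baseline, week 6 and week 12 without making it conditional on staying in treatment. Rules for missing data and definitions of the analysis sets may well be in the full protocol (Ethics approval cites version 4) or in an analysis plan. Their absence from an article is not an error.

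The size is open to challenge too. Every dropout rate, correlation and SD above is assumed, and the plan does not single out week 6 as the primary comparison.

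These objections stand against the categorical reading. They do not remove the narrower point. The main text gives the t-test to the secondary outcomes and an ANOVA or ANCOVA to the RPQ. Of the two ordinary ways to fit that ANOVA, one conflicts with intention-to-treat and the other mishandles repeated scores. The fit that avoids both is not the one named.

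**Conclusion.** The point holds in conditional form. A classical repeated-measures fit removes participants missing week 12, discards their valid pre-crossover RPQ and reduces intention-to-treat to completers. An ordinary one-row-per-visit fit keeps the values but gets the error structure wrong. On either reading a better method is available in the named software.

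The loss of precision is modest: about 5 percentage points of power (76% against 71%), assuming 10% loss per period and that 50 participants give 80% power. Bias could be anything from none to about a third of the target effect (8.0 down to 5.2). The upper end needs strongly informative leaving in opposite directions by group, for which the article gives no evidence. The change is worth making because it is cheap and protects the cleanest randomised comparison in the trial.

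**What to change.** For the intention-to-treat analysis of the RPQ, replace the ANOVA with a likelihood-based mixed model for repeated measures (SAS PROC MIXED). Fit sequence, visit and their interaction, with correlated errors within person, using every available RPQ from all randomised participants. State that the week-6 comparison does not depend on attending week 12. Report withdrawals by sequence and period.

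If the full protocol does not already say so, add that the week-6 and week-12 RPQ are still requested from participants who stop a programme, unless they withdraw consent.

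The cost is a few sentences and a different procedure in software already chosen. The model relies on data being missing at random given the observed scores. That is weaker than what a complete-case ANOVA needs, but it does not protect against leaving that depends on unobserved outcomes.
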